### Eligibility criteria

#### Inclusion criteria

To fulfil the inclusion criteria the participants must fulfil two of four criteria from the questionnaires, and one of two from the physical tests.

#### Questionnaires

Pain intensity ≥ 3 on the Numeric Pain Rating Scale (NPRS)Sumscore > 30 measured with Örebro Musculoskeletal Pain Questionnaire short form (ÖMPQ-SF)Neck Disability Index (NDI) > 14Shoulder Pain and Disability Inventory (SPADI) > 20

#### Physical tests

≥ 6 tender points according to the American College of Rheumatology criteria for FibromyalgiaSumscore ≥ 7 from five movement tests from the Global Physiotherapy Examination (GPE-Flexibility)

#### Exclusion criteria

Sick-listed more than 6 months continuously

### Intervention

#### Norwegian Psychomotor Physiotherapy (NPMP) (A)

NPMP was developed in the late 1940s as a result of the collaboration between the physiotherapist Aadel Bülow-Hansen (1906–2001) and the psychiatrist Trygve Braatøy (1904–1953). The treatment approach is based on the premise that the whole body reacts to physical and psychological strain. Over time this may affect flexibility in the body, ability to relax, muscle tension, respiration, posture and body awareness. These elements will also interact [8].

The patient’s history and social situation, as well as the body examination of posture, respiration pattern, movements, muscle quality, autonomic reactions and body awareness, form the basis for the treatment process. The treatment is process-oriented and focusing on the whole patient. The aim is to readjust the posture and the muscle tension by means of breath-releasing massage, touch and movements adapted closely to the patient’s reaction. Movements include grounding (body awareness training in standing and walking), balancing, stretching and relaxation. To increase the patient’s sensation of muscle tension and function, verbal reflections on body experiences is also emphasised and addressed during treatment [8] (Table 3). Consequently, NPMP is not a standardized treatment but rather a continual pragmatic treatment, adjusted to the patient’s bodily experiences and reactions [8]. Each session last for 45–60 min, and is usually received once a week, sometimes every second week.

**Table 3 Tab3:** Fundamental principles of the two interventions

Norwegian Psychomotor Physiotherapy (NPMP)	Cognitive Patient Education and active individual Physiotherapy (COPE-PT)
NPMP is specialization at post-graduate master level for physiotherapists	COPE is taught to PTs during a 3 days course
Key elements in NPMP	The education program has three basic elements
• Readjust posture	• Reduction of what the patients
• Harmonize muscle tension	• perceive as threatening inputs to the brain
• Harmonize breathing	• Targeting the patients’ own understanding of the pain
• Harmonize movements	• Exposure to the threatening inputs
• Body awareness	
• Each treatment session last 45–60 min	• Each education session last 30 min
• Once a week or every second week	• Education once a week for 4 times
• For 3–6 months	• Followed by active, individualized physiotherapy according to pain problems once a week or every second week
	• For 3–6 months

#### Cognitive Patient Education and active physiotherapy (COPE-PT) (B)

COPE is an “intensive neurophysiology education” program developed by a group of British and Australian researchers as an education program for patients with low back pain. The theory behind the program is primarily based on the neurophysiology of pain, reflected by sensitization and neuronal response to inactivity and movement control [21]. Accordingly, the cognitive elements of the educational program consist of an understanding of pain that differs from the traditional “injury model”, and instead focuses on learning the patient how to better cope with pain and fear of movement.

Studies have documented an additional effect of COPE when combined with physiotherapy [22–24]. In the present study the educational package will be adjusted to patients with extensive musculoskeletal pain or patients with neck and shoulder pain (Table 3). The patients will receive one session weekly with COPE, given by a physiotherapist, maximum four times, followed by active, individualized physiotherapy (PT), as needed and wanted by the patient. The active part of the intervention, usually consist of supervised exercises, and details will be recorded by the PTs.

COPE-PT is thus more an educational package given in a cognitive enhancing manner, followed by active exercise therapy, in contrast to the more process-oriented, body awareness approach found in NMPM, given through massage, relaxation and breathing techniques and exercise, as well as in the dialogue between therapist and patient. As the treatment approaches are pragmatic, number of sessions and content may vary, and the different therapists will register this throughout. Further details can be found in the Additional file 1.

### Baseline and outcome measures

Different measurements will be used at baseline and follow-up in order to detect potential changes both in pain, physical function, mental health condition and quality of life (Tables 1 and 2).

### Primary outcome

The primary outcome is pain, assessed by the *Numeric Pain Rating Scale (NPRS)* which assesses average pain intensity the last 2 weeks on a scale ranging from 0 (no pain) to 10 (worst). The scale has shown better reliability and responsiveness than the visual analogue scale [25].

### Secondary outcomes

The secondary outcomes include additional questionnaires and several physical tests:

#### *Questionnaires* (Table 1)

The *Örebro Musculoskeletal Pain Questionnaire short form (ÖMPQ-SF)* has shown to predict the risk for future work disability. The short form with 10 items is appropriate for clinical and research purposes, and is nearly as accurate as the longer version [26].

The *Neck Disability Index (NDI)*, measures disability due to neck pain, and is a modification of the Oswestry Disability Index [27]. Good reliability and validity of NDI have been demonstrated [27].

The *Shoulder Pain and Disability Inventory (SPADI)* [28], is developed to measure current shoulder pain and function. SPADI has shown to have good reliability, good construct validity [29], to be responsive to change over time in a variety of patient populations, and is able to discriminate adequately between patients with improving and deteriorating conditions [29, 30].

The *Norwegian Function Assessment Scale (NFAS)*, is questioning work-related functioning with basis in the ICF’s classification system [31]. Test-retest reliability has been tested in a normal population and found acceptable [32].

*Subjective Health Complaints Inventory (SHC)* consists of items regarding subjective somatic or psychological complaints experienced during the last month. The SHC inventory has shown satisfactory test-retest reliability in students and patients with LBP [33].

The *Hopkins Symptoms Checklist (HSCL-25)* measures anxiety and depression symptoms. The HSCL has been shown to have satisfactory validity and reliability in psychiatric outpatients and in a normal population [34].

The *Tampa Scale of Kinesiophobia (TSK)* [35] in short form measures fear of movement and re-injury. The TSK has been validated in numerous studies including patients with neck pain, acute and chronic LBP and fibromyalgia [35–38].

The *Short Form-12 (SF-12)*, which is a 12-item version of the SF-36, measure physical and mental health-related quality of life [39]. The SF-12 has shown good internal consistency, validity, and responsiveness in patients with LBP [40].

The *Bergen Insomnia Scale (BIS)* measures sleep disturbance. BIS can refer to high internal consistency, adequate reliability and good convergent and discriminative validity [41].

Sick leave will be measured by number of self-reported days of absence from work.

At 3 and 6 months the patients in both arms of the RCT will also fill in the *Client Satisfaction Questionnaire (CSQ-8)* [42].

#### *Physical tests* (Table 2)

Six tests from the *Global Body Examination (GBE)* assess truncal flexibility and ability to relax during passive movements. Discriminating ability between healthy and different patients groups has shown to be very good to excellent [43]. Good inter-tester reliability has been demonstrated in a former version of the GBE [44].

*Back Performance Scale* (BPS), consists of five tests reflecting mobility-related activities for trunk and lower extremities and include a sock-test, a pick-up test, a roll-up test, a fingertip-to-floor test and a lift test where a box weighing 4 kg (women) or 5 kg (men) is lifted from floor to waist for 1 min) [45, 46].

A *high lift test* is a test quite similar to the lifting test in the Back Performance Scale (BPS).

Static endurance of the back extensors is assessed with *the Biering–Sørensen test* [47]. Test-retest reliability has been reported as satisfactory, but variability has been high [48–50].

Abdominal strength is assessed with a three levels *dynamic sit-up test* with increasing demands for each level [51, 52].

*The American College of Rheumatology* (ACR) of fibromyalgia has defined *18 tender points* [53]. In addition to counting the number of tender points, the examiner gets an impression whether pain is localized or widespread. A pain drawing is also used for this.

Recently an inter-tester reliability study of all the physical test have been performed, showing high to very high reliability of all the tests (ICC2,1 from 0.80 to 0.94) [54].

### Sample size calculation

The aim is to enroll a total of 128 participants in the study. Power calculations are based on a power of 80 % and a significance level of 5 % to detect a meaningful difference between the two intervention groups on the patient-reported primary outcome measure. Based on previous studies using the NPRS to measure pain intensity, a clinically significant difference can be estimated to be approximately 2 points with a standard deviation of 2. Power calculations based on these data indicate that a total of 16 participants in each group will be sufficient to detect a treatment difference after ended intervention. However, long term follow-up (12 months) and expectations of decrease in difference between the two intervention groups with 1 point, there is a need to increase each group to 64 participants.

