### Follow-up

All the participants will be followed-up at three different points. At 3 and 12 months questionnaires will be sent to the participants’ home address, and returned by them in a pre-paid envelop. At 6 months the participants will undergo a functional examination and fill inn questionnaires (the same as at baseline) (Table 2 and 3). A receptionist makes the 6 months follow-up appointments, and a blinded physiotherapist, not knowing what treatment the patient has been given, will perform the examination (Fig. 1).

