### Statistical analysis

All statistical analyses will be carried out using R version 3.2.5 (The R Foundation for Statistical Computing, www.r-project.org) and SPSS version 24 (SPSS Inc., Chicago, IL, USA) for windows. All tests will be two-sided, and *p* values less than 0.05 will be considered statistically significant.

Continuous variables will be reported as means ± SEM and categorical variables as percentages (%) ± SEM. The chi-square test will be used to test for group difference in percentages of categorical variables, while the two-sample *t*-test will be used to test for group difference in means of continuous variables. Analog non-parametric tests will be evaluated when strongly skewed distributions.

To estimate and compare the treatment effect of the two specific interventions at the four time points (baseline, 3, 6 and 12 months) we will use mixed effects models. All models will define treatment, time and treatment-by-time interaction as fixed effects, whereas a random intercept will be specified to account for correlated observations of the same individual (an exchangeable correlation structure assumed). Depending on the measurement level of the outcome under study, treatment effects will be presented as relative estimates (e.g., odds ratios, relative risk) or predicted mean differences with 95 % confidence intervals, corrected for multiple testing. Age, gender, body mass index, duration of pain and work status will be evaluated as additional adjustment variables.

We cannot exclude the possibility that missing outcome data may occur for a proportion of participants. The mixed effects model will produce unbiased effect estimates as the model uses a likelihood-based estimation procedure, provided the data are missing at random (MAR). Additionally, a multiple imputation method for missing data will be utilized if missing data occur in covariates as well.

Effect size (ES) for mean change will also be calculated by subtracting post-test scores (6 and 12 months) from baseline in the two groups, dividing it by the standard deviation (SD) of the change score.

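### Enrolment of 64 per group equals the number of complete 12-month observations needed, so the stated 80% power for a 1-point difference holds only with essentially no loss to follow-up

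*Protocol article*

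**What the plan says.** All of this is in the protocol article.

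- **Sample size calculation.** "The aim is to enroll a total of 128 participants in the study". The design values are "Power calculations are based on a power of 80 % and a significance level of 5"%, and "a clinically significant difference can be estimated to be approximately 2 points with a standard deviation of 2". From these the section finds that "a total of 16 participants in each group will be sufficient to detect a treatment difference after ended intervention". It then supposes that the difference shrinks by 1 point by 12 months and concludes that "there is a need to increase each group to 64 participants". It mentions no allowance for loss.
- **Statistical analysis.** "All tests will be two-sided". On missing data: "We cannot exclude the possibility that missing outcome data may occur for a proportion of participants". The planned model is a mixed model with baseline, 3, 6 and 12 months as outcome time points, a treatment-by-time interaction and a random intercept.
- **Follow-up.** "At 3 and 12 months questionnaires will be sent to the" participants' homes, so the 12-month NPRS depends on postal return.
- **Background.** The one earlier randomised trial of NPMP, given in groups, is described as having a large drop-out in the treatment arm. No figure is given.

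**The concern.** The number to be enrolled and the number that must be analysed at 12 months are the same. The sample size paragraph mentions long-term follow-up just before raising the group size from 16 to 64, so a reader could take the increase as partly an allowance for attrition. If it is not, the plan claims 80% power for its sizing comparison only on the condition that almost everyone returns the 12-month questionnaire, and it does not state that condition.

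This bears on interpretation. The trial compares two active treatments, and a non-significant 12-month result is a realistic outcome. It would be read against a nominal 80% power that the design delivers only with nearly complete data.

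**Working it through.** **Inputs from the article.** Difference 2 points after the intervention and 1 point at 12 months; SD 2; 5% significance, two-sided; 80% power; two groups of similar size; 64 enrolled per group.

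**Step 1: reproduce the plan's figures.** By the normal approximation, n per group = 2 × SD² × (1.960 + 0.842)² / difference², where (1.960 + 0.842)² ≈ 7.849.

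- 2 points: 2 × 4 × 7.849 / 4 = 15.7, rounded up to 16. The exact t-test gives 16.7; 16 per group has 78.1% power.
- 1 point: 2 × 4 × 7.849 / 1 = 62.8, rounded up to 63. The exact t-test gives 63.77, rounded up to 64; 64 per group has 80.1% power.

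Both stated sizes are reproduced. A one-sided test would need about 50 per group for 1 point, so the plan's figure is the two-sided one.

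**Step 2: what the rise from 16 to 64 pays for.** Sample size varies with 1/difference². Halving the difference multiplies n by 4, and 16 × 4 = 64. Nothing is left over for attrition.

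**Step 3: complete-case power with 64 enrolled.** The article gives no loss rate, so the rates below are assumptions. Analysed n per group = 64 × (1 − loss); two-sample t-test, 1 point, SD 2.

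| Assumed loss at 12 months | Analysed per group | Power for 1 point | Difference detectable with 80% power |
|---|---|---|---|
| 0% | 64 | 80.1% | 1.00 |
| 5% | 60.8 | 78.1% | not calculated |
| 10% | 57.6 | 75.8% | 1.05 |
| 20% | 51.2 | 70.7% | 1.12 |
| 30% | 44.8 | 64.8% | 1.20 |

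Very small losses matter little: 63 per group gives 79.5% and 62 gives 78.9%.

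**Step 4: power under the planned mixed model.** A participant missing only at 12 months still contributes baseline, 3 and 6 months. Assume an exchangeable correlation of 0.5 and arm means that are free at every time point. The three earlier visits then explain R² = 3 × 0.5² / (1 + 2 × 0.5) = 0.375 of the 12-month variance. The variance of the 12-month contrast is multiplied, relative to complete data, by (1 − R²)/(1 − loss) + R².

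| Assumed loss, at 12 months only | Variance factor | Effective n per group (64 / factor) | Power, normal approximation | Power, t-test |
|---|---|---|---|---|
| 10% | 0.625/0.9 + 0.375 = 1.069 | 59.8 | 78% | 77% |
| 20% | 0.625/0.8 + 0.375 = 1.156 | 55.4 | 75% | 74% |
| 30% | 0.625/0.7 + 0.375 = 1.268 | 50.5 | 71% | 70% |

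The model recovers part of the loss, but power stays below 80%. The gain disappears for participants who leave before any follow-up visit.

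**Step 5: what baseline adjustment could add.** By the simple ANCOVA formula the SD becomes 2 × √(1 − r²), where r is the correlation between baseline and 12 months (assumed; the article gives none).

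| r | SD after adjustment | Power at 20% loss | Power at 30% loss |
|---|---|---|---|
| 0.4 | 1.83 | 78% | 72% |
| 0.5 | 1.73 | 82% | 77% |
| 0.6 | 1.60 | 88% | 83% |

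**The case against.** The strongest reply has four parts.

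1. **The sums are right and the article is condensed.** It is true that 64 per group is reproduced, so this is not a calculation error. But the article presents a complete calculation and sets enrolment equal to its result. What is at fault is the unstated condition on the 80%, not an omitted detail.

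2. **The protocol does not predict drop-out.** A reader might infer from the missing-data paragraph and from the earlier group trial that the authors themselves expect substantial loss. The text does not support that: it only declines to rule missing outcomes out, and gives no rate. The earlier trial was of group treatment and no figure is quoted. Postal collection is not evidence of any particular rate either. Every loss rate used here is therefore an assumption.

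3. **Any loss at all destroys the power.** This is another tempting reading, and it is too strong. Losing one or two participants per group costs about 1 percentage point. The shortfall becomes material from roughly 5 to 10% loss.

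4. **The mixed model handles missing data.** The article claims unbiased estimates if data are missing at random. That addresses bias and does not replace lost information. Part of the objection stands: the complete-case figures are pessimistic when loss is confined to 12 months, as Step 4 shows. They are about right when participants leave before any follow-up.

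It is also fair that the 2-point difference after the intervention keeps more than 99% power even with 30% loss, and that the plan reports confidence intervals, from which a null result can be read directly. The point is confined to the 1-point comparison at 12 months, but that comparison is the one that set the sample size.

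**Conclusion.** The point holds in this limited form. Enrolment of 64 per group leaves no margin: it is the number of complete 12-month observations required for 80% power at 1 point, SD 2 and two-sided 5%. With an assumed 10/20/30% loss at 12 months, power is about 76/71/65% by complete-case t-test. It is about 78/75/71% under the planned mixed model if loss is at 12 months only and the correlation is 0.5 (about 1 percentage point lower by the t distribution). The detectable difference on the complete-case basis rises to 1.05/1.12/1.20 points.

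The absence of any margin follows from the article's own figures. The size of the shortfall rests on assumed loss rates and correlations. These calculations do not count any effect of the planned multiple-testing correction or of clustering by therapist.

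**What to change.** **Power statement.** Keep 128 and restate what it delivers, for example: 64 per group gives 80% power for a 1-point difference only with complete 12-month data; with an assumed 20% loss, complete-case power is about 71%, and the difference detectable with 80% power is 1.12 points. The sponsor should supply and justify the loss rate.

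**Baseline NPRS.** Use it for precision in one coherent way. The plan already treats baseline as an outcome time point, so adding it as a covariate to that model would use it twice. Choose one of:

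- keep baseline as an outcome row and constrain the two arms to a common baseline mean; or
- enter baseline NPRS as a covariate and model only 3, 6 and 12 months as outcomes.

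On the ANCOVA figures above, this gives about 78 to 88% at 20% loss for correlations of 0.4 to 0.6. It offsets much of the shortfall but does not assure 80%: at 30% loss with a correlation of 0.4, power is 72%.

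**Cost.** A less favourable power statement and a small, pre-specified change to the model. No extra participants are needed. For comparison, restoring 64 complete observations per group by enrolment alone would take 64/0.9 = 71.1, so 72 per group (144 in total, rounded up to an even number) at 10% loss, or 64/0.8 = 80 per group (160 in total) at 20%.

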### Randomization method

Block randomization of the study sample will be employed, using a computer generated list with blocks of six to ensure similar number of participants in both intervention groups. Information about intervention allocation (A or B) is then put into premade and ordered envelopes. The sealed envelopes are kept in a locked box by receptionists who have no information about the content. The receptionist hands out one envelop consecutively to the participants after eligibility and baseline measurements. The envelope contains information regarding treatment and names of treating therapists (A or B), and the participants are invited to call one of them for an appointment.

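### A constant, stated block size of six in one list makes up to a quarter of allocations certain in the worst case; varying and withholding the sizes would greatly reduce this at almost no cost

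*Protocol article*

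**What the plan says.** The Randomization method section of the protocol article describes block randomization, "using a computer generated list with blocks of six to ensure similar number of participants in both intervention groups". It mentions neither strata nor variation in block size.

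The same section gives several safeguards. The envelopes are prepared beforehand, ordered, sealed and locked away, and the receptionists who hold them do not know what is inside. On timing it says: "The receptionist hands out one envelop consecutively to the participants after eligibility and baseline measurements". The envelope tells the participant the treatment and the names of the therapists, and the participant then contacts one of them.

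The design is called single blind. The only blinding described is that of the physiotherapist who performs the 6-month examination (Follow-up section). Participants and therapists therefore know the treatment. The planned size is given in the Sample size calculation section: "The aim is to enroll a total of 128 participants in the study", that is, 64 per arm.

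**The concern.** Sealing and locking stop anyone from reading the next envelope. They do not stop someone from working out its content from the envelopes already opened. Under a constant block size, the last place in every block is always fixed by the five before it, and the fourth and fifth places sometimes are. Because treatment is open, each allocation is known to the participant and the treating therapist soon after it is made. The size itself is printed in the article.

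What is at stake is selection at entry. Under the Eligibility criteria, every participant must meet at least one of two examiner-administered physical criteria (tender points or flexibility). Under Participants, the second consent is taken in the same consultation, before randomization. Handing over the envelope only after these steps protects against foreknowledge only if the next allocation cannot be predicted while they are under way.

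**Working it through.** **Inputs.** Block size 6, one list, similar arm sizes (Randomization method). I take this as three A and three B per block. Total 128, 64 per arm; difference of 1 point at 12 months, SD 2, 80% power, 5% level (Sample size calculation); two-sided tests (Statistical analysis).

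**The plan's own figure.** A two-sample t-test for a 1-point difference with SD 2 needs 63.77 per arm, so 64. The stated size is reproduced, and this point does not affect it.

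**Certain allocations, constant blocks of six.** There are 20 equally likely arrangements of three A and three B. A place is certain once one arm's three envelopes are used up.

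- Places 1 to 3: never certain.
- Place 4: the first three must be alike, 2/20 = 10%.
- Place 5: the first four must contain all three of one arm, 8/20 = 40%.
- Place 6: always, 100%.

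The sum is 0.1 + 0.4 + 1.0 = 1.5 per block, which agrees with 2m/(m+1) for m = 3. That is 1.5/6 = 25%. Since 128 = 21 × 6 + 2, the trial total is 21 × 1.5 = 31.5, or 31.5/128 = 24.6%.

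**Best guess, constant blocks of six.** Guessing the arm used less often so far (a coin toss if equal) is right with probability 0.5, 0.6, 0.6, 0.7, 0.7 and 1.0 at places 1 to 6. The sum is 4.1, and 4.1/6 = 68.3%. Over 128 it is (21 × 4.1 + 0.5 + 0.6)/128 = 87.2/128 = 68.1%.

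**Varying sizes.** Lists of 128 were simulated (1000 per scheme, sizes equally likely) for an observer who knows the set of sizes and every earlier allocation and updates by Bayes' rule.

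| Sizes | Certain | Best guess right | Largest final difference between arms |
|---|---|---|---|
| 6 only | 24.6% | 68.1% | 2 |
| 4, 6 | 5.5% | 69.2% | 2 |
| 4, 6, 8 | 2.4% | 67.9% | 4 |
| 6, 8, 10 | 1.7% | 66.3% | 4 |

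Certainty falls by about a factor of ten with 4, 6 and 8. The best guess hardly moves, for a simple reason. Completed blocks are balanced, so the running count over the whole list equals the count within the current block, and the rule of guessing the less-used arm needs no block sizes. Its success in blocks of 4, 6 and 8 is 70.8%, 68.3% and 66.6%. Weighted by length this gives (4 × 0.708 + 6 × 0.683 + 8 × 0.666)/18 = 68.1%. Withholding the sizes therefore takes away certainty; it does not by itself bring the guess of someone with the full history down to 50%.

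**Cost in power.** By the t-test, 64:64 gives 80.15% and 62:66 gives 80.11%.

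**The case against.** The strongest reply is that the article shows nobody who could make the deduction. It would take the block boundaries and the complete run of earlier allocations. The envelopes are held by people unaware of their content, nothing says they are opened in front of staff, and five therapists per arm each see only part of one arm. This stands, and it makes 25% an upper limit and not an estimate. It does not dispose of the point, because the article also does not say that eligibility assessors are kept unaware of earlier allocations.

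Room for steering entry is also limited. Two of four questionnaire thresholds must be met as well, and the physical tests have numeric cut-offs with reported inter-tester reliability of 0.80 to 0.94. That stands too.

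A reader might infer three stronger things that the documents do not support.

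- That the reception holding the envelopes also learns allocations through the follow-up bookings. The Follow-up section says only "A receptionist makes the 6 months follow-up appointments". It does not say this is the same reception, and booking a visit need not reveal the arm.
- That the 6-month examiner could work out the arm from enrolment order. This would require the boundaries and the other allocations in the block, and the article states that the examiner does not know the treatment. The examiner performs the physical tests, which are secondary; the primary pain score is reported by the patient.
- That varying the block size abolishes predictability. The table above shows that it does not.

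Finally, blocks of six with sealed envelopes contradict nothing else in the article. That is why this is an improvement to a stated choice and not an error.

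**Conclusion.** The point holds in a limited form. The article fixes and states a constant block size of six in a single list with no strata named, in a trial with open treatment. For an observer with full knowledge, 25% of allocations per block (31.5 of 128) would be certain. The share that anyone at enrolment could actually deduce is unknown and may be nil; the documents do not support saying that a quarter of allocations are in fact deducible.

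The figures assume three of each arm per block, equally likely sizes in the varying schemes, and an observer who knows every earlier allocation. Recruitment status at publication is not given, so the practical effect of having printed the size is also unknown. The importance is minor. The case for change rests on its very low cost.

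**What to change.** Generate the list with randomly varying block sizes, for example 4, 6 and 8. If recruitment is open, do this for the unused part of the list. Withhold both the individual sizes and the set of sizes from clinic staff, receptionists, therapists and examiners until recruitment ends, and do not print them before then. Because a guess from the running count needs no sizes, also state that those who assess eligibility are kept unaware of earlier allocations. If recruitment is complete, report who knew the block size and the earlier allocations.

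The cost is one new computer list and repacking of unused envelopes. At 128 participants the final difference between arms could reach 4 (62:66) instead of at most 2, a loss of 80.15 − 80.11 = 0.04 percentage points of power.
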